**FIGURE 3 F3:**
[figure not shown]
Power calculation. The sample size estimate is based on changes in our primary outcome, AAQ-II. The figure illustrates a power curve function to explore trade-offs between power and sample size. The analysis showed that a significant difference between the experimental group and the active control group require at least 35 participants (to have 93% power) in each group. Error bars = standard deviation.

### Ethical Considerations

The project has been ethically approved by the Regional Ethical Committee in Stockholm (Dnr. 2018/2057-31) and follows the Declaration of Helsinki. The included patients will provide signed written consent. The collected data will be handled according to the general data protection regulation (GDPR), and according to applicable legislation to ensure an optimal protection of patients’ security. Pseudonymization will be used. Project-specific identifiers will be assigned to all participants and those IDs are to be used throughout the study. A lookup key file that links the Project ID to the participant’s personal identity number will be kept in a secure server at Karolinska Institutet, Division of Clinical Geriatrics, Department of Neurobiology, Care Sciences, and Society were the chief investigator works together with the other main researchers.

Cognitive impairments are often related to a progressive decline in cognitive and intellectual abilities. There is therefore a risk that patients may progress in their decline during the period in which they partake in the present study. Clinicians in the project will need to be watchful on potential progression and initiate a referral to other health care units that may be needed if the patient’s condition worsens. The intervention might in some cases be perceived as psychologically and emotionally challenging, for instance, the behavioral change part. This is not unique for the current study but is often a part of any psychological clinical treatment. In addition, there may be patients that experience frustration or are disappointed by a (lack of) improvement, in relation to their expected gains following treatment. These potential negative side effects of participation will be systematically monitored and addressed professionally. To provide quality-assured support to the patients, clinicians (licensed or under supervision to be licensed), psychology students under clinical training or psychology graduated (MSc) assistants will interact with the participants. Most of them will be licensed and sanctioned by the Social Board of Health and Welfare (Socialstyrelsen) and therefore expected to follow the ethical guidelines to protect the patients and their personal information.

The targeted patient group is seldom offered any psychological treatment or support as part of their clinical routine. Therefore, from an empirical perspective, we cannot identify any known disadvantages of participation in the present study. Rather, the present study provides a new venue of treatment/rehabilitation methods that has been completely lacking for these patients. Potential benefits should therefore outweigh the potential risks for the individual when partaking in the present study.

Thus, we consider that the present design has minimal risk for these participants.

### Amendments

We have not yet decided the method for analyzing the measures derived from blood and saliva, this will be decided in collaboration with experts in the field and researchers from outside the present research group. As soon as the analytical strategy for evaluating the biological measures are decided, we will update this information on ClinicalTrials.gov. In case of additional amendments to the present study protocol, which might impact patient safety, ethical aspects, or scientific evaluation of the trial, we will submit a protocol amendment to the Regional Ethical Committee in Stockholm and await their approval. Furthermore, our trial registry in ClinicalTrials.gov will be updated.

### Adverse Events

An adverse event is generally defined as an event that occurs during the research project that results in a worsening of symptoms for the participants, i.e., that involves somatic or psychological harm. Clinical (psychologist and MD) judgment will decide the level of seriousness of a potential adverse event according to standard clinical practice. In addition, a deterioration in the outcome measures can be defined as indicative of adverse events. All adverse events will be reported. In case of a more serious adverse event, we will consult our psychiatric expert, and referral to specialist health care will be conducted as deemed appropriate.

### Insurance

Insurance coverage will be provided by Landstingets Ömsesidiga Fond (LÖF) that is a Swedish insurance company whose main task is to insure publicly financed health care providers. If a patient suffers an injury while in the research study, the injury will be evaluated by LÖF and may result in financial compensation according to the Patient Injury Act.

### Statistical Analysis

#### Strategy for the Main and Secondary Hypotheses Analyses

The continuous longitudinal data derived from the RCT will be analyzed using appropriate growth models (e.g., LMM) that in addition to studying change at the group level also can: model change on the individual level; flexibly incorporate time-varying predictors; handle dependency for repeated observations and provide correct estimates with missing data under largely unconstrained missing data conditions (Hesser, 2015). As a default strategy we will use LMM to analyze the condition by time interaction and will follow established recommendations for model specification and reporting results (Bolger and Laurenceau, 2013). In the main analysis, we will compare intervention change between the PIPCI group and the active control group. However, we will also compare the PIPCI group and the active control group with the waiting list group. An alpha level of 0.05 and a 95% CI will be used to evaluate the main and secondary analyses. Regarding the LMM-analyses, assumptions relating to the normal distribution of residuals and homogeneity of variance will be assessed, respectively, based on visual evaluation of a histogram of model residuals, as well as by a plot of the model fitted values against the residuals from the model.

#### Strategy for the Exploratory Research Questions

##### Question 1

In addition to using the growth model framework to investigate predictors of intervention outcomes, we will also apply non-linear models using machine learning methodology, such as support vector machines (SVMs). The SVM fits the separating hyperplane with support from the cases that lie closest to each other in hyperspace but which are of different labels, the support vectors. The SVM is therefore less sensitive to outliers than the classic linear model. Moreover, by transforming the hyperplane with a non-linear kernel, the SVM can also separate (classify) non-linearly separable classes. The developed risk models will mainly predict cognitive test measures (neuropsychological assessments), and biological markers (visual ratings derived from magnetic resonance imaging, and cerebrospinal fluid dementia measures.

##### Question 2

The qualitative approach will be conducted in line with consolidated criteria for reporting qualitative research (COREQ) (Hayes et al., 2006), with the aim to examine in-depth participant’s experiences of participation in the RCT. Interviews will be conducted with participants in the study after the long-term follow-up. Interviews will be digitally recorded and transcribed, and content analysis will be used in the analysis (Graneheim et al., 2017).

##### Question 3

The QALY calculation will be evaluated by the change in AAQ-II induced by the treatment multiplied by the duration of the treatment effect to provide the number of QALYs gained (Prieto and Sacristán, 2003). QALYs will then be incorporated with medical costs to generate a final common denominator of cost.

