#### Secondary Hypotheses

1.The secondary hypotheses state that participants receiving PIPCI will improve psychological health (stress measures, quality of life, depression, and general health), and increase their telomerase activity compared to participants in the active control group and the waiting list control group.2.An additional secondary hypothesis state that participants receiving PIPCI, and participants in the active control group, will improve on the cognitive test measures compared to the waiting list group. However, we do not have any directed hypothesis comparing PIPCI and the active control group.

Exploratory research questions (without any directed hypotheses)

1.Can we identify significant pre-intervention predictors for intervention outcomes?2.How do participants perceive the intervention?3.Is PIPCI cost-effective and does it impact health-economic variables?

The current protocol article aims to provide a description of the conceptual model behind the novel psychological intervention manual as well as specific information on the study design, materials and methods.

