### Outcome for the Pre- and Post-evaluations

#### Primary Outcome Measures

•Psychological health measures: Our primary outcome measure is psychological flexibility measured with the total score of the AAQ-II (Bond et al., 2011). This outcome is motivated by the fact that psychological flexibility is the essential target of our psychological intervention and has a strong history of evidence, as detailed in the introduction.

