#### Secondary Outcome Measures

•Psychological health measures: Stress-related symptoms reported with the Perceived Stress Scale (PSS) (Lee, 2012), depressive symptoms with the Becks Depression Inventory (BDI) (Dozois et al., 1998), quality of life with the Brunnsviken Brief Quality of Life Scale (BBQ) (Lindner et al., 2016), and general health with the Short Form Health Survey (SF-36) (Ware, 2000).•Cognitive functions: Executive functions with the Color-Word Interference Test (CWIT) and the Trail Making Test (TMT) from Delis-Kaplan Executive Function System (D-KEFS) (Delis et al., 2001), non-verbal episodic memory with the Brief Visuospatial Memory Test-Revised (BVMT-R) (Benedict et al., 1996), attention/working-memory with Digit-Span from the Wechsler Adult Intelligence Scale (WAIS-IV) (Wechsler, 2008), and the computer-based AX-Continuous Performance Task (CPT) (Braver and Cohen, 2000), processing speed with Digit-Symbol from WAIS-IV (Wechsler, 2008), and psychomotor speed with the Deary-Liewald Reaction Time Task (D-LRTT) (Deary et al., 2011).•Biological health measures: Telomerase (the enzyme involved in maintaining telomere length, among other things) activity by modified real-time telomeric repeat amplification protocol (Hou et al., 2001). This outcome is motivated by previous research showing that biological measures, such as telomere length are related to aging and differences in such biological marker has been coupled with differences in the prevalence of psychiatric, cognitive, and somatic conditions (Han et al., 2019). Telomerase activity may also be associated with improvement to psychological treatment (Månsson et al., 2019). In addition, we will also evaluate saliva measures of cortisol, testosterone, adrenocorticotropic hormone (ACTH), and dehydroepiandrosterone (DHEA) (Kalman and Grahn, 2004).•Costs-effectiveness: Health-economic impact is measured in Quality Adjusted Life Years (QALY’s) (Torrance and Feeny, 1989).

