#### Reliability and Validity of Outcome Measurements

For AAQ-II the mean alpha coefficient for the items is 0.84 and the scale has shown acceptable test-retest reliability (0.79–0.81) (Bond et al., 2011). PSS has repeatedly shown alpha coefficients of >0.70 and the test-retest reliability has been assessed in four studies and met the criterion of >0.70 in all cases (Lee, 2012). BDI-II has shown high internal consistency with alpha coefficient >0.90, furthermore, it has shown adequate validity in terms of diagnostic discrimination as well as validity in terms of factorial and content validity (Dozois et al., 1998). BBQ has shown satisfactory reliability both in terms of inter-item correlation and Cronbach’s alpha, as well as regarding test-retest reliability in the short term. An intra-class correlation coefficient of 0.82, indicate high test-retest reliability (Lindner et al., 2016). The SF-36 is a well-validated and reliable scale that often reaches alpha coefficients of >0.80, and has been used in multiple settings and shown both discriminatory and predictive ability (Ware, 2000). For the cognitive measures, information regarding reliability and validity are referred to in the test manuals above. For the biological measures, the analytical methods are yet to be decided, but we aim to employ methods with adequate psychometric properties.

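### QALYs are defined as AAQ-II change times duration, but AAQ-II is a psychological-flexibility score with no stated conversion to a utility, so the product is not a QALY

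*Protocol article*

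**What the plan says.** All places are in the protocol article.

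- Secondary Outcome Measures, cost-effectiveness entry: "Health-economic impact is measured in Quality Adjusted Life Years". No instrument for the quality weight is named there.
- Secondary Hypotheses, third exploratory question: "Is PIPCI cost-effective and does it impact health-economic variables". No directional hypothesis is attached to it.
- Strategy for the Exploratory Research Questions, Question 3, gives the rule: "The QALY calculation will be evaluated by the change in AAQ-II induced by the treatment multiplied by the duration of the treatment effect". The stated purpose of the product is "to provide the number of QALYs gained". The next step is: "QALYs will then be incorporated with medical costs to generate a final common denominator of cost".
- Primary Outcome Measures describes the primary endpoint as "psychological flexibility measured with the total score of the AAQ-II".
- Reliability and Validity of Outcome Measurements gives internal consistency (alpha 0.84) and test-retest reliability (0.79–0.81) for AAQ-II, and nothing on preference weights or utilities.
- SF-36 is listed among the secondary outcomes as a measure of general health. It is not linked to the QALY calculation.

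**The concern.** The quality term in a QALY has to be a utility: a preference-based number on a scale where 0 is dead and 1 is full health. Only then is a utility difference multiplied by years a quantity of healthy time. A questionnaire total in points has neither the anchors nor the preference weighting, so multiplying it by years gives point-years.

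This is a method the article states, not a detail left to a later plan. The sentence names the weight, the multiplier and what the product is called. If it is followed, the trial would publish a number of QALYs, and a ratio of cost to that number, that could not be compared with QALY results from any other study. The size of the number would depend on how AAQ-II happens to be scored and not on how much health was gained.

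**Working it through.** The article states no QALY, utility or cost figure, so there is nothing to reproduce. The check is one of units and limits.

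**Inputs from the article**
- Quality term: AAQ-II change, with no conversion stated (Question 3).
- AAQ-II: a total score for psychological flexibility (Primary Outcome Measures).
- Last assessment: 6-month follow-up, after 10 weekly sessions (RCT Assessments; RCT Design and Groups).

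**Assumed, because the article does not give them**
- Size of the AAQ-II change, c: 0.5 to 10 points.
- Duration of effect, T: 0.5 year, or 10 weeks plus 6 months = 10/52 + 0.5 = 0.692 year.
- Utility gains of 0.02, 0.05 and 0.10, and an incremental cost of 1000 units.

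**Step 1: ceiling for a true QALY gain.** The gain is (u1 − u0) × T. With u1 at most 1 and u0 at least 0, it cannot exceed T.

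**Step 2: the article's rule.** The result is c × T, in point-years. Its ratio to the ceiling is (c × T) / T = c. The ratio does not depend on T, so any change above 1 point exceeds the ceiling whatever duration is used.

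| AAQ-II change (assumed) | Rule, T = 0.5 | Ceiling | Rule, T = 0.692 | Ceiling |
|---|---|---|---|---|
| 0.5 | 0.25 | 0.5 | 0.346 | 0.692 |
| 1 | 0.5 | 0.5 | 0.692 | 0.692 |
| 2 | 1.0 | 0.5 | 1.385 | 0.692 |
| 5 | 2.5 | 0.5 | 3.462 | 0.692 |
| 10 | 5.0 | 0.5 | 6.923 | 0.692 |

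A change of 1 point or less stays within the ceiling, but it is still in point-years and is no more a QALY than the others.

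**Step 3: what real QALY gains might look like.** For the assumed utility gains over 0.5 year:
- 0.02 × 0.5 = 0.010
- 0.05 × 0.5 = 0.025
- 0.10 × 0.5 = 0.050

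**Step 4: effect on a cost ratio.** With the assumed cost of 1000 units:
- Article's rule, 5 points over 0.5 year: 1000 / 2.5 = 400 per nominal QALY.
- Utility gain 0.10: 1000 / 0.050 = 20,000 per QALY.
- Utility gain 0.02: 1000 / 0.010 = 100,000 per QALY.

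With these values the rule makes the intervention look far cheaper per unit of health. The cost and utility figures are illustrations only. The conclusion rests on the units in Steps 1 and 2.

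**The case against.** The strongest defence is that this is one exploratory analysis in a condensed article. The rule cites a methods source that is not at hand, and a conversion to utility may have been intended. The 5 points and the 0.5 year are assumed, the ceiling of 0.5 holds only from a non-negative starting utility, and the article mentions no cost-per-QALY threshold. All of that is fair as to size. It does not rescue the sentence, which says that the direct product gives QALYs gained; no passage supplies a conversion.

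A reader might infer more than the article supports:

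- *That question 3 as a whole cannot be answered.* It also asks about health-economic variables, and health care costs are evaluated in their own right. Neither needs the QALY formula. AAQ-II could also serve as the effect unit of a ratio labelled as such.
- *That the economic result merely rescales the efficacy result.* Only the effect term is tied to AAQ-II. Duration is a separate multiplier, and costs are separate data.
- *That the trial's main result is at risk.* The primary AAQ-II comparison, the sample size and the randomization do not use the QALY rule, and no numbered hypothesis depends on it.
- *That SF-36 is certain to be available at all three assessments.* The article gives three assessment times in general, but the measure-by-time schedule is in a figure not shown, and SF-36 is listed under a heading that refers to the pre- and post-evaluations. SF-36 at 6 months is plausible, not confirmed. Its version and a value set are not given either.

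**Conclusion.** The point holds for the QALY weight. As written, the rule yields AAQ-II point-years, and the QALY entry among the secondary outcomes and the cost-per-QALY part of exploratory question 3 would be invalid. The result overstates the largest possible gain by a factor equal to the AAQ-II change in points whenever that change is above 1. This follows from the units and needs no assumed effect, only that raw points are used, as the sentence says, and that starting utility is not negative. The specific figures (2.5 against 0.5; 400 against 20,000 to 100,000) rest on the assumptions listed with them.

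Severity is moderate: the method is wrong as stated and no other QALY method is offered, but the analysis is exploratory.

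**What to change.** Rewrite the Question 3 rule so that AAQ-II change is no longer the QALY weight. There are two acceptable routes.

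1. **Keep QALYs.** Name a preference-based utility as the source of the weight. An index derived from the SF-36 already collected is one candidate, provided that its version permits this and that it is administered at the assessments needed; confirm both first. Compute QALYs as the area under the utility curve over the available assessments, adjusted for baseline utility. That adjustment agrees with the article's general intention to adjust outcomes for the pre-intervention value.
2. **If no usable utility exists.** Drop the QALY label, amend the secondary outcome entry to match, and report cost per AAQ-II point.

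The cost is a change of wording and, for the first route, one scoring step. If the SF-36 is suitable and scheduled as needed, no new data are required. The drawback is that the QALY gain will be smaller and less precise than the stated rule would suggest. AAQ-II stays as the primary efficacy endpoint in either case.

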#### Sensitivity Analyses

Importantly, in line with the intention-to-treat principle, all available randomized participant data will be analyzed using maximum likelihood estimation, an approach that uses information from all available observations to estimate parameters and provides unbiased estimates and standard errors in the presence of incomplete data under the assumption that data are missing at random. Appropriate sensitivity analyses will be performed to assess the robustness of the findings, and to identify possible key limitations, e.g., the effects of dropout.

### Dissemination Policy

We will communicate our research findings via several channels:

•Research articles in high impact scholarly journals•National and international research collaborations•Presentations at local unit meetings, and hospital committee meetings•Presentations at national or international conferences.•Presentations at patient organizations•Communication to patients and their close ones at the clinical settings•Via media communication, such as press releases•Validation studies of our research findings at other research units/hospitals.

## Discussion

The main purpose of this article was to introduce the novel psychological intervention (PIPCI) manual and to report the study protocol for evaluating the intervention. We consider the present study methodology adequate to generate reliable and valid results on feasibility, intervention effects, and predictions of outcome based on symptomology and biomarkers.

Cognitive medicine is a new but emerging field intersecting the health-care sciences and neuroscience. Cognitive medicine aims to uncover diverse cognition-related disease mechanisms, with an overarching focus on how to cope with or to prevent cognitive decline (Wallin et al., 2018). The development and evaluation of a feasible and effective psychological intervention manual has the potential to provide a new intervention as well as important information regarding non-pharmacological treatments for a common and many times debilitating somatic condition that affect the afflicted individual, significant others, the local community and the society at large. If the psychological intervention shows positive effects on life satisfaction, psychological health, biological changes, and healthcare costs, it will have important implications on the future healthcare of patients with early CIs that are at risk of developing dementia.

To prevent falsely positive trial effects, an active control group will be recruited. It is important to include a placebo-like condition so that the experimental group does not have a better prognosis than the comparison group for reasons other than the hypothesized effects of the intervention during the study (Van De Ven et al., 2016). The active control intervention is related to cognitive training and we cannot neglect the possibility that the active control group improves similarly to, or even better (especially on the cognitive measures) than the experimental group which will receive PIPCI. Thus, a strength of our study design is the control condition, which increases the possibility to draw causal conclusions of not only intervention effect but also intervention specificity.

In a later phase, the evaluated psychological intervention has the potential to be disseminated and scaled to group-, and/or internet-based administration, as well as delivered in hybrid modalities including both face-to-face (in individual and/or group settings) and internet-based elements. This could make the intervention more available for individuals that cannot easily visit adequate healthcare facilities and could potentially also increase the cost-effectiveness of the intervention. We will not consider cognitive MCI-subtypes at the inclusion occasion. However, we will evaluate if cognitive MCI-subtypes predict intervention outcomes. Cognitive subtype in this regard refers to the pattern of impairments across the cognitive domains and is not a specific diagnosis. SCD or MCI can be due to any underlying condition. Finally, a future prospect is also to evaluate the psychological intervention for those that struggle with adherence to the FINGER intervention to increase motivation to perform lifestyle changes.

